# Neurostimulation for cognitive rehabilitation in stroke (NeuroCog): study protocol for a randomized controlled trial

**DOI:** 10.1186/s13063-015-0945-1

**Published:** 2015-09-29

**Keywords:** Transcranial direct current stimulation, Cognitive rehabilitation, Clinical trial

## Abstract

**Background:**

Stroke patients may present severe cognitive impairments, primarily related to executive functions. Transcranial direct current stimulation has shown promising results, with neuromodulatory and neuroplastic effects. This study is a double-blind, sham-controlled clinical trial aiming to compare the long-term effects of stimulation in two different cognitive regions after a stroke.

**Methods/Design:**

Sixty patients who suffer from chronic strokes will be randomized into one of four groups: dorsolateral prefrontal cortex, cingulo-opercular network, motor primary cortex and sham stimulation. Each group will receive transcranial direct current stimulation at an intensity of 2 mA for 20 minutes daily for 10 consecutive days. Patients will be assessed with a Dysexecutive Questionnaire, Semantic Fluency Test, categorical verbal fluency and Go-no go tests, Wechsler Adult Intelligence Scale, Rey Auditory-Verbal Learning Test, Letter Comparison and Pattern Comparison Tasks at baseline and after their tenth stimulation session. Those who achieve clinical improvement with neurostimulation will be invited to receive treatment for 12 months as part of a follow-up study.

**Discussion:**

Long-term stimulation could be analyzed in regard to possible adaptive changes on plasticity after structural brain damage and if these changes are different in terms of clinical improvement when applied to two important cognitive centers.

**Trials registration:**

Clinicaltrials.gov, NCT02315807. 9 December 2014.

## Background

Because cerebrovascular diseases are considered a major factor of mortality and morbidity in many parts of the world, new therapeutic methods have been proposed for the management of cognitive sequelae after a stroke. However, few studies have examined cognitive factors associated with treatment by neurostimulation after a stroke. More emphasis has been directed at functional improvement related to outcomes such as mobility, independence and daily living activities [1]. In contrast, it is estimated that 75 % of people will have losses in executive functions after a stroke. These difficulties cause problems in their abilities to perform day-to-day tasks and deal with other problems such as movement disorders, which are also derived from their brain injury [2].

Neurostimulation techniques such as transcranial magnetic stimulation (TMS) and transcranial direct current stimulation (tDCS) have shown promising results in this population [3]. Both techniques can lead to an improvement of lost skills/abilities, with virtually no side effects or discomfort for patients [4]. Regarding tDCS, there are numerous advantages compared to other non-invasive brain stimulation therapies, such as low cost, easy handling and high portability. During the application of electric current, essential neurostimulatory effects are observed. After stopping tDCS application, neuroplastic effects can be observed [5].

With regard to the stimulation site of cognitive areas, it is not yet clear what role each area would play during the planning and execution of cognitive information [6]. Although the dorsolateral prefrontal cortex (dlPFC) is considered the main cognitive control area used in experiments with tDCS [7], neuroimaging techniques have contributed to identifying other “multiple functional neural networks,” which may be related to processing or cognitive control categories [8]. A study involving mapping and interconnection of various regions showed that the frontoparietal network could serve as a “flexible hub” that would alter connectivity with other neural networks based on the specific task [9]. Other authors indicate that the parietal component seems to initiate and adjust the control, while the cingulo-opercular network (CON) provides a stable maintenance of the task, suggesting connections between two core networks and other weaker long-range connections between components [10].

In this respect, some aspects of cognition can be broadly generalized, and there is no agreed upon list of all components comprising executive functions (as an example). This results in discrepancies between the studies concerning which the factors should be related [11, 12].

To address the theoretical gaps, we propose that the cingulo-opercular network could serve as an alternative locus of stimulation for cognitive rehabilitation of these patients. Combined with this, this work represents the first controlled clinical trial involving the application of tDCS on stroke. It will include a follow-up of 12 months, making it possible to investigate not only the effects that occur in the short term, but also those that last for a longer period after neurostimulation. In a recent study that evaluated cognitive problems after strokes in young patients (<50 years), it was found that “mental slowness” occurs up to 10 years after brain injury, and so it is necessary to assess the presence of cognitive deficits after a long period of follow-up [13].

Thus, the objective of this study is to 1) evaluate the efficacy of tDCS on two different networks, the frontoparietal (specifically in the dlPFC) and the cingulo-opercular (anterior insula/frontal operculum), comparing them with each other for cognitive rehabilitation after a chronic stroke; 2) check whether there are differences between the benefits achieved by stimulation of these two cortical areas and how big these differences are; and 3) present the study protocol, the previous results of the clinical trial, ensuring adherence and compliance with the guidelines previously proposed.

## Methods/Design

### Design

A clinical double-blind, randomized, controlled trial will be performed involving patients with chronic stroke, randomly assigned to four groups: Group 1) active tDCS in fronto-parietal region (dlPFC); Group 2) active tDCS in the cingulo-opercular region-CON (anterior insula/frontal operculum); Group 3) active tDCS in the primary motor cortex (M1); and Group 4) sham tDCS in M1. This region was used as a place of active and placebo control.

Initially, all participants will undergo 10 consecutive daily sessions of neurostimulation (excluding weekends). Evaluations will be conducted pre- and post-test (T0 and T1, respectively). After 1 month, the participants will be checked to see who attained clinical improvement with treatment: that is, those patients who had a final score (T2) on the Dysexecutive Questionnaire (DEX) greater than at least 2.77 standard error of measurement compared from their baseline/initial testing [14]. Those who have an adequate response will be invited to receive treatment for 12 months. In this period of follow-up, the stimulation sessions will be applied twice monthly, for 5 consecutive days. This model is similar to another that has already been applied/used by other authors with positive results in a study involving tDCS for treatment of depression in order to assess whether the benefits of regularly performed neurostimulation continue in the long term [15]. Adverse effects will be computed periodically to prevent possible deleterious effects (see Fig. 1, which demonstrates the flow of the study). Previous studies have demonstrated that tDCS induces minimal discomfort sensations, such as mild tingling and itching sensations under the electrodes, predominantly in the first few seconds of the tDCS [16, 17].

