### Procedures

The primary outcome of the study will be the Dysexecutive Questionnaire (DEX) [34], composed of 20 subtests, standardized, with total score ranging from 0 to 80 points, applied to the patient and a family member. The issues involve disturbances in executive functions such as emotional or personality, motivational, behavioral and cognitive changes. It is an instrument with ecological validity confirmed for patients with brain injuries and may provide important information on executive functions with implications for cognitive rehabilitation [35].

Secondary outcomes will be: the Semantic Fluency Test (FAS), which assesses the recall of words that begin with a certain letter and category fluency for the generation of words in a semantic class [36]; Go-no go, which tests self-monitoring, inhibition, initiation and cognitive flexibility [37]; Wechsler Intelligence Scale for Adults (WAIS), in the subtests of digit symbol coding, matrix reasoning, comprehension and letter-number sequencing for evaluation of executive functions [38]; Rey Auditory Verbal Learning (RAVLT) test that measures recent memory, learning, interference, retention and recognition memory [39]; Letter Comparison and Pattern Comparison Tasks [40].

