### Statistical analysis

To determine the number of participants in each group, we will apply the proposed criteria for clinical trials. As observed in previous studies using the DEX for cognitive evaluation, we found that the average obtained by individuals with cognitive decline (without presence of dementia) undergoing rehabilitation protocols lies in a range of 15 to 17 points, with a deviation-pattern of 5.0 to 8.0 points [41–43]. The minimal importance difference will be considered based on the variation of the standard error of measurement approach, considering 1 for a small effect, 1.96 for a moderate and 2.77 for a large effect [14]. From these criteria, considering 90 % power and taking into account possible dropouts, we calculate a final sample size of 90 participants. A significance level of *P* <0.05 will be considered.

An analysis of intention to treat will be used, and sensitivity analysis will be performed with different allocation procedures to verify the strength of the data. The best strategy resulting from the comparison of the following methods will be chosen: last observation carried forward, complete-case analysis, likelihood-based methods and multiple imputation.

For the primary endpoint, we will use a mixed linear model. We will model the change in cognitive performance according to the DEX using the covariates of time, group and interaction between treatment and time. The covariance with repeated measures and for each patient will also be measured. For secondary outcomes, repeated measures analysis of variance (ANOVA) will be used in which the dependent variable is the performance in each cognitive test and the independent variables are group (dlPFC, CON, M1, or sham), treatment time (baseline/initiation, week 2 and follow-up) and interaction group × treatment time. If necessary, post-hoc comparisons using Bonferroni correction will be made.

Deleterious and adverse cognitive effects will be calculated in terms of the proportion in each group and in each period, and will be analyzed by the Fisher exact test.

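### The 12-month phase admits only patients who respond on the primary outcome, so it cannot support the stated comparison of long-term effects between stimulation sites

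*Protocol article*

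**What the plan says.** The abstract presents the trial as "aiming to compare the long-term effects of stimulation in two different cognitive regions after a stroke". The Background section rests the longer-term question on the 12-month phase: "It will include a follow-up of 12 months, making it possible to investigate not only the effects that occur in the short term".

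The Design section sets the entry rule. "After 1 month, the participants will be checked to see who attained clinical improvement with treatment". The criterion is a "final score (T2) on the Dysexecutive Questionnaire (DEX) greater than at least 2.77 standard error of measurement compared from their baseline/initial testing". It continues: "Those who have an adequate response will be invited to receive treatment for 12 months". The abstract has the same rule: "Those who achieve clinical improvement with neurostimulation will be invited to receive treatment for 12 months as part of a follow-up study".

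The selection instrument is also the main endpoint. Under Procedures: "The primary outcome of the study will be the Dysexecutive Questionnaire (DEX").

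The Statistical analysis section names an intention-to-treat analysis. For DEX it specifies a mixed linear model with time, group and their interaction, and lists no time levels. For the secondary outcomes it specifies a repeated-measures ANOVA with group and "treatment time (baseline/initiation, week 2 and follow-up"). It does not say whether the last level is T2 or the 12-month phase, and it does not mention that only responders enter that phase.

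**The concern.** Randomisation makes the four arms comparable as whole groups. The gate at 1 month keeps patients according to a value of the primary outcome measured after treatment has begun to act. If the sites differ in effect, the arms pass different proportions of patients. Those who pass are also selected to look alike, because each has cleared the same threshold on the same scale. A difference between arms among entrants at 12 months is then neither the randomised effect nor an unbiased estimate of it, and it will usually be pulled towards zero. The risk is that a small difference among responders is reported as randomised evidence that the two sites have similar long-term effects.

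**Working it through.** **Passages side by side.** The aim is a between-site comparison of long-term effects (abstract). The only long-term element is the 12-month phase (Background, Design). Entry requires a T2 change on the primary outcome of at least 2.77 standard errors of measurement (SEM). No second randomisation and no 12-month visit for non-responders is described. So the patients described as being observed long term are not the groups that randomisation formed. There is no figure in the plan to reproduce on this point. What follows is an illustration.

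**Inputs from the article:** entry threshold of 2.77 SEM; DEX SD 5.0 to 8.0 points (8 used first); 60 patients allocated 1:1:1:1, so 15 per arm. **Assumed, not in the article:** reliability r of 0.8 or 0.9; T0–T2 correlation ρ of 0.6, 0.7 or 0.8; true mean improvement μ of 6 points active and 2 sham (true difference 4); normal scores; true state unchanged from T2 to month 12; fresh measurement error at month 12. Improvement is coded positive.

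**Formulas.**
- SEM = SD × √(1 − r); threshold = 2.77 × SEM.
- SD of the T0–T2 change: s = SD × √(2(1 − ρ)).
- Proportion passing: p = 1 − Φ(z), with z = (threshold − μ)/s.
- Mean T2 change among those passing: m = μ + s × φ(z)/p.
- Mean month-12 change in the same patients: μ + b(m − μ), with b = (s² − SEM²)/s², because the T2 error does not recur at month 12.

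**One case in full (ρ = 0.7, r = 0.9).** SEM = 8 × √0.1 = 2.53; threshold = 7.01; s = 8 × √0.6 = 6.20; b = (38.4 − 6.4)/38.4 = 0.833.
- Active: z = (7.01 − 6)/6.20 = 0.16; p = 43.5%; m = 11.60; month 12: 6 + 0.833 × 5.60 = 10.67.
- Sham: z = (7.01 − 2)/6.20 = 0.81; p = 21.0%; m = 10.51; month 12: 2 + 0.833 × 8.51 = 9.09.
- Difference among responders: 1.1 points at T2 and 1.6 at month 12, against a true 4.0.

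**All six cases, SD 8:**

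| ρ | r | Threshold | Active passing | Sham passing | Responder difference, T2 | Responder difference, month 12 |
|---|---|---|---|---|---|---|
| 0.6 | 0.8 | 9.9 | 29% | 13% | 0.9 | 1.7 |
| 0.6 | 0.9 | 7.0 | 44% | 24% | 1.1 | 1.5 |
| 0.7 | 0.8 | 9.9 | 26% | 10% | 0.8 | 1.9 |
| 0.7 | 0.9 | 7.0 | 44% | 21% | 1.1 | 1.6 |
| 0.8 | 0.8 | 9.9 | 22% | 6% | 0.7 | 2.4 |
| 0.8 | 0.9 | 7.0 | 42% | 16% | 1.0 | 1.8 |

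Of 15 per arm this is about 3–7 active and 1–4 sham entrants. With the 90 participants given under Statistical analysis (22.5 per arm) it is about 5–10 and 1–5.

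**Sensitivity.** With SD 5 and the other assumptions unchanged, 48–70% of active and 9–30% of sham patients pass, and the month-12 difference among responders is 1.7–2.5 of 4 points. A separate simulation assumed SD 5 and 8, reliability 0.7–0.9, a between-patient spread of true change of 0.3 SD, no sham effect, and active effects of 1.96 or 2.77 SEM. It retained 47–56% of the true difference among responders, and following all randomised patients recovered the whole of it. In an arm with no true change at all, the pass rate is 1 − Φ(2.77/√2) = 2.5%, so 15 such patients yield no entrant with probability 0.975^15, about 68%.

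**The case against.** The best defence is that the article may never intend a 12-month arm comparison. Design describes three assessments (T0, T1 after ten weekday sessions, and T2 at 1 month), and these map one to one onto the ANOVA's baseline, week 2 and follow-up. On that reading every randomised patient contributes and the last level precedes selection. The abstract calls the 12-month phase a follow-up study, and Design links it to whether benefits persist, which is a fair descriptive question among responders. The numbered objectives in Background and the primary objective in Discussion do not mention long-term effects. Finally, the gate governs invitation to treatment. The flow chart is not available here, and if the full protocol assesses everyone at 12 months, arms could be compared as randomised strategies without this bias.

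Much of this stands, and it limits the point. A reader might infer that the ANOVA's follow-up level is the 12-month visit and should be deleted. The text does not settle that, and deletion could remove a valid all-patient comparison at T2. A reader might also infer a headline 12-month DEX comparison of all four arms. No passage states one: the abstract names two regions, and the time levels are listed only for secondary outcomes. Nor should the 0.7–1.1 points among responders at T2 be read as the 12-month result, since that is the truncated selection variable itself.

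What the defence does not remove is the abstract's aim. If follow-up means T2, no between-arm analysis described serves that aim. If it means 12 months, the analysis conflicts with intention to treat. Nothing in the article labels the 12-month phase descriptive or non-randomised.

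**Conclusion.** The point holds for the 12-month phase only. As described, that phase cannot deliver a randomised comparison of long-term effects between sites, because entry depends on a post-randomisation value of the primary outcome. The T0, T1 and T2 comparisons remain randomised. The structural conclusion needs no numerical assumption. The size does: at SD 8 and under the assumptions listed, 22–44% of active and 6–24% of sham patients enter, and a true 4-point difference appears as about 1.5–2.4 points among responders at month 12. The DEX reliability, T0–T2 correlation, treatment effects and course after T2 are all assumed, so these figures show direction and order of magnitude and are not a forecast.

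**What to change.** - In Statistical analysis, state that the follow-up level is T2 and keep it, for all randomised patients.
- Limit randomised between-arm inference to T0, T1 and T2.
- Report 12-month responder data within each arm, labelled as a non-randomised description of durability.
- If a long-term arm comparison is wanted, use the proportion of all randomised patients per arm who responded at T2 and still meet the threshold at 12 months, counting T2 non-responders as failures.
- Reword the aim in the abstract, and the matching sentence in Background, to agree.

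These are changes of wording and analysis only, and none alters treatment. The price is a narrower long-term claim: durability among responders, or sustained response by arm, in place of a comparison of long-term mean effects.

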**Fig. 1 Fig1:**
[figure not shown]
Flow chart of study. ASB: Assessment of Stroke and other Brain Damage; CES-D: Center for Epidemiological Studies-Depression; CON: cingulo-opercular network; DEX: Dysexecutive Questionnaire; dlPFC: dorsolateral prefrontal cortex; FAS: Semantic Fluency Test; DRS-2: Dementia Rating Scale-2; LCPCT: Letter Comparison and Pattern Comparison Tasks; M1: primary motor cortex; MOCA: Montreal Cognitive Assessment; NIHSS: National Institute of Health Stroke Scale; OLT: Object Learning Test; RAVLT: Rey Auditory-Verbal Learning Test; tDCS: transcranial direct current stimulation; TMT: Trail Making Test; WAIS: Wechsler Adult Intelligence Scale

The method of randomization will be 1: 1: 1: 1, with interchange between blocks generated by an online program (random.org). Concealed allocation will be used with numbered, opaque-sealed sequential envelopes so that the person responsible for allocation will not be in contact with patients or with the work of others. All examiners will be blind to the type of treatment the patient is receiving (site of stimulation) and other assessments that will be carried out. The efficiency of the masking/blinding mechanism will be evaluated at the time of the last interview with the evaluators. They will state what region they believe the patient received stimulation in. Patients will also be blinded with a masking evaluation carried out on the last post-test where they will try to guess in which region stimulation was applied: the main (dlPFC) or secondary area (CON) of cognitive control, the motor control region (M1) or sham stimulation.

Attrition will be considered when a) three alternating or two consecutive absences; b) presence of cognitive comorbidities throughout the trial; c) loss during follow-up. There will be adherence strategies administered such as being able to make up an absence the following week, and offering flexible schedules and frequent contact through phone calls confirming dates of procedures and reinforcing the importance of treatment compliance.

The study was approved by the Health Sciences Centre Ethical Committee (#30163714.0.0000.5188) and is governed according to the principles of the Declaration of Helsinki. To conduct the study, the informed consent of each participating patient will be collected. The protocol follows all the recommendations of the Standard Protocol Items: Recommendations for Interventional Trials Statement (SPIRIT) 2013 [18].

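### Repeated absences and new cognitive comorbidity are counted as attrition alongside true loss to follow-up; this needs reconciling with the intention-to-treat analysis

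*Protocol article*

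**What the plan says.** The attrition rule is in the Design section of the protocol article, in the text after Figure 1: "Attrition will be considered when a) three alternating or two consecutive absences; b) presence of cognitive comorbidities throughout the trial". Loss to follow-up comes after these as a separate item (c). The adherence strategies that follow it include "being able to make up an absence the following week".

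The Statistical analysis section states: "An analysis of intention to treat will be used". It gives a mixed linear model for the DEX. For missing data it names four candidates, "last observation carried forward, complete-case analysis, likelihood-based methods and multiple imputation", and says: "The best strategy resulting from the comparison of the following methods will be chosen". It also plans to compare deleterious cognitive effects between groups, by period, with the Fisher exact test.

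The Procedures section describes the content of the DEX: "The issues involve disturbances in executive functions such as emotional or personality, motivational, behavioral and cognitive changes".

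The article does not say that patients classed as attrition are dropped from the analysis. It also does not say that they are still assessed, or that data collected after the event are used.

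**The concern.** Item (c) already covers patients who are lost. Items (a) and (b) therefore add patients who may be available for assessment at T1 and T2.

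- **Item (a)** is non-adherence after randomisation. Under intention to treat, such patients stay in their arm and their outcome is wanted.
- **Item (b)** depends on cognition after randomisation. It lies close to what the DEX measures and may be affected by treatment. It may also overlap with the deleterious cognitive effects to be compared between arms, so one event could be both a safety result and a reason to count the patient as a dropout.

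If either item ends outcome collection, the plan itself creates missing data, and whether a value is missing depends on adherence or on cognitive course. Arms that differ in tolerability, perceived benefit or cognitive deterioration would then lose different kinds of patients. The four groups are small, so a few such losses can move an arm mean.

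**Working it through.** The plan gives no figure on this point, so there is none to reproduce. The check is of wording, followed by illustrations whose inputs are partly assumed.

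**1. The passages side by side.**
- Items (a), (b) and (c) are alternatives under one label. Because (c) is separate, (a) and (b) are not defined by missing outcome data.
- Intention to treat calls for outcomes from all randomised patients, in the arm assigned. The rule does not say whether outcomes are still sought after (a) or (b).
- The Participants section excludes severe cognitive comorbidities at entry, supported by cut-offs on three scales. Item (b) omits the word severe and gives no cut-off, so what triggers it is open to judgement.
- An absence may be made up, but the text does not say whether a made-up session still counts towards the limit in (a).

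**2. Would the listed methods repair the loss?**
- Complete-case analysis drops patients without later data.
- Last observation carried forward fixes the DEX at its value before the event.
- Likelihood methods and standard multiple imputation assume that missingness depends only on observed data. That is doubtful if assessment stops because cognition worsened before the worsening was recorded on the DEX.

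**3. Shift in an arm mean (illustration).** Inputs: 15 per arm, from the 60 patients in the Abstract and Participants section (60 / 4); DEX SD of 5.0 to 8.0 from Statistical analysis; and, as assumptions, 2 patients removed, each 8 points from the arm mean in the same direction.
- Shift = 2 × 8 / (15 − 2) = 16 / 13 = 1.23 points.
- In SD units: 1.23 / 8.0 = 0.15 to 1.23 / 5.0 = 0.25.
- The effect on a treatment comparison depends on the arm. Removing worsening sham patients flatters sham and works against stimulation; removing worsening active patients does the reverse.

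**4. How many patients could meet item (a) (illustration).** The randomised phase has 10 sessions. Assume independent absences with probability p per session and that made-up sessions do not cancel an absence. All 2^10 patterns were enumerated, counting those with two absences in a row or at least three in total.

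| p | Share meeting (a) | Of 60 | Of 90 |
|---|---|---|---|
| 2% | 0.4% | 0.2 | 0.4 |
| 5% | 2.6% | 1.6 | 2.4 |
| 10% | 10.9% | 6.5 | 9.8 |
| 15% | 23.5% | 14.1 | 21.1 |

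**5. Power (illustration).** The plan's large effect is 2.77 standard errors of measurement, so d = 2.77 × √(1 − r), where r is the reliability of the DEX. The plan does not state r, so a range is assumed. The test is a two-sided two-sample t-test at 0.05 for one pair of arms, with 20% of each arm contributing nothing: 15 × 0.8 = 12, and 90 / 4 × 0.8 = 18.

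| r | d | n = 15 | n = 12 | n = 18 |
|---|---|---|---|---|
| 0.70 | 1.517 | 98% | 94% | 99% |
| 0.80 | 1.239 | 91% | 83% | 95% |
| 0.90 | 0.876 | 64% | 54% | 72% |

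The columns for 15 and 12 rest on 60 patients. The column for 18 rests on the 90 given in Statistical analysis, where a dropout allowance is said to be included. The loss of power therefore runs from slight to material, depending on inputs that the plan does not settle.

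**The case against.** The strongest reply is that attrition is only a label. A reader might infer from the rule that these patients are removed and that the plan contradicts intention to treat. The documents do not support that reading: nothing says that assessment stops, that data are discarded or that anyone leaves the analysis set. Counting dropouts and then analysing as randomised are compatible, and a mixed model can use the partial data that patients provide. This part of the reply stands.

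Second, a journal article may leave the handling of such patients to a fuller document. That is fair for operational detail. Here, however, the article does state a rule, and the rule places non-adherence and a cognitive event on the same footing as loss to follow-up.

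Third, a reader might see a clash between the absence limit and the make-up provision. The text does not establish one. An occasional miss could be made up while repeated misses count towards the limit. What remains is an ambiguity about how made-up sessions count.

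Fourth, in the Participants section cognitive comorbidity means diagnosed conditions, not a worse DEX score, so item (b) should not be read as covering every patient whose cognition declines. This also stands. Even so, a diagnosed cognitive condition arising after randomisation is close to the outcome, and item (b) carries no threshold.

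Finally, likelihood methods and multiple imputation do handle missingness explained by observed data. It would be too strong to say that no listed method could help. The supportable statement is that they would not reliably do so, particularly as the method is to be chosen only after comparison.

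**Conclusion.** The point holds as a conflict to be reconciled. The rule classes potentially assessable patients as attrition on adherence and on a post-randomisation event close to the DEX. On the ordinary meaning of the word, that creates avoidable and possibly informative missing data under a declared intention-to-treat analysis. Exclusion from the analysis is not stated and should not be presented as fact.

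The size cannot be established from the documents. The shift of about 1.2 DEX points (0.15 to 0.25 SD) rests on an assumed two removals at 8 points each in an arm of 15. The power figures rest on an assumed reliability, an assumed 20% loss and one of two stated sample sizes, so no single figure should be quoted from them. The case for change rests on the wording and the low cost of the remedy. The change should be made soon, because recruitment is under way and assessments not done cannot be recovered.

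**What to change.** - Define attrition, for analysis purposes, as missing outcome data only.
- Record items (a) and (b) as non-adherence or intercurrent events, and define cognitive comorbidity in (b).
- State that neither item ends outcome assessment: continue to collect the scheduled T1 and T2 DEX from these patients and analyse it in the assigned arm.
- Use the absence limits only to define a per-protocol sensitivity analysis.
- Reconcile the absence count with the make-up provision by stating how a made-up session is counted. What the limit itself should be is for the investigators.

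The cost is a change of wording and a small extra effort to bring these patients to visits already scheduled.
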